### Secondary outcomes

The secondary outcome measures are:Difference in mean percent time in target (4–10 mmol/L) range at 12 months between the study groups (from data downloaded from the r-CGM device).Difference in mean diabetes-specific distress at 12 months between the study groups as measured by the Problem Areas in Diabetes (PAID) scale [16].Incremental cost per quality-adjusted life year (QALY) for the intervention relative to control for the trial period, as measured by the EuroQol 5 dimension 3 levels (EQ-5D-3 L) [17].Difference in mean HbA1c (%) at 6 months between the intervention and control groups.

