### Outcome measures

The primary outcome, HbA1c, will be measured by venous blood test in an accredited laboratory. Time in the target range will be calculated as the percentage of time blood glucose levels remain between 4 and 10 mmol/L as measured by the r-CGM device. Diabetes-specific distress will be measured using the PAID scale [16]. This scale consists of 20 questions relating to negative emotions associated with diabetes, with five possible responses to each question: 0 = no problem, 1 = minor problem, 2 = moderate problem, 3 = somewhat serious problem, and 4 = serious problem. The 20 items are summed, and the total is multiplied by 1.25 so that total score ranges from 0 to 100. Higher scores indicate greater levels of diabetes-specific distress; a score of ≥ 40 indicates severe diabetes distress [20]. The PAID measure has high internal reliability and validity [16].

Results from the EQ-5D-3 L assessment at each measurement will be transformed into utility scores using Australian preference weights [21]. An average utility curve, which measures the mean quality of life trajectory for patients, will be derived by interpolating between baseline and the follow-up measurement points [22]. QALYs will then be estimated for both the intervention and the control group using the ‘area under the curve’ method [23]. As the economic evaluation will be performed within a 12-month period, discounting will not be applied.

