### Statistical analysis

#### Sample size

The sample size is based on an individually randomised controlled trial without accounting for stratification by clinic. Clinical significance was considered to be a difference of at least 0.5% (7 mmol/mol) in mean HbA1c between the groups and is based on current guidelines which recommend intensification of therapy when HbA1c levels remain 0.5% (7 mmol/mol) above target [19]. The sample size was calculated using HbA1c in %. Using a significance level of 0.05, power of 0.8, clinically significant difference of 0.5%, and standard deviation of 1.3% for HbA1c [24], the required number of participants in each group is 108, a total of 216. This is equivalent to a difference in the mean HbA1c of 7 mmol/mol between the groups with a standard deviation of 14 mmol/mol [24]. Assuming a 20% attrition rate, the required sample size inflates to 270 (135 in each group). Allowing for 10% clinic attrition and assuming six participants per clinic, we require 50 clinics with six participants per clinic (150 in each group).

Figure 1 shows the minimum number of clinics and participants per clinic required for 20% participant attrition and 10% clinic attrition. The figure shows that it is possible to recruit 300 participants in a variety of ways; for example, 25 clinics with 12 participants per clinic, 30 clinics with 10 participants per clinic, 50 clinics with six participants per clinic, and 75 clinics with four participants per clinic. Four participants per clinic was the minimum recommended to allow for estimation of the correlation in outcome measure between participants in the same group and clinic. From prior knowledge of recruitment patterns from the Stepping Up Study [24] it was decided to recruit 50 clinics with six participants per clinic.

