##### Economic evaluation

A within trial economic evaluation using participants’ Medicare costs, pharmaceutical benefit schedule (PBS) costs, hospitalisation costs, self-reported costs, diabetic outcomes (proportion with controlled diabetes, HbA1c ≤ 7 mmol/mol) and quality of life data will be performed using a decision analytic framework [29]. The economic model will construct costs and quality of life associated with the health states ‘controlled diabetes’, ‘uncontrolled diabetes’, and ‘death’. It will be constructed in STATA statistical software [25] based on the original trial data and will utilise linear and generalised linear modelling techniques to determine a cost per QALY gained. The analysis will be conducted from a health system and societal perspective. Costs and benefits will be bootstrapped. The distribution of costs and benefits will be simulated using a probabilistic analysis. The results of the economic modelling will be presented as the mean and 95% confidence interval (CI) of the incremental cost per QALY gained at trial conclusion for the r-CGM study group relative to the control group. Simulated cost-effectiveness will be presented for r-CGM relative to the control via a cost-effectiveness plane and a cost-effectiveness acceptability curve. Univariate and probabilistic sensitivity analyses will be performed to assess uncertainty. Estimates of projected implementation costs across Australia will be estimated.

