**Table 5 Tab5:** Mean and standard deviation (SD) costs, mean and SD quality-adjusted life years (QALYs), mean differences and incremental cost-effectiveness ratios during the trial follow-up period for intervention vs control groups (secondary analyses)

	Intervention mean (SD)				Control mean (SD)		Mean difference (95% CI) per patient			*P* value
Costs										
Intervention (A)										
Hospital utilization (B)										
Medical benefits (C)										
Pharmaceuticals (D)										
Patient costs (E)										
Total cost health system (A + B + C + D)						(1)				
Total cost societal (A + B + C + D + E)						(2)				
QALYs						(3)				
Incremental cost effectiveness ratio (ICER)										
Health system perspective						(1)/(3)				
Societal perspective						(2)/(3)				

*CI* confidence interval

**Table 6 Tab6:** Estimated glycated haemoglobin (HbA1c) and between-group differences by history of severe hypoglycaemia and personalised HbA1c target for intervention and control groups (sub-group analyses)

	Estimated mean HbA1c (95% CI)				Difference in estimated mean HbA1c and HbA1c target		Unadjusted		Adjusted^a^	
	Intervention group (*n*=)		Control group (*n*=)		Intervention group (*n*=)	Control group (*n*=)	Intervention vs. control between-group differences (95% CI)	*P* value	Intervention vs. control between-group differences (95% CI)	*P* value
Severe hypoglycaemia										
History of severe hypoglycaemia^b^										
Baseline										
6 months										
12 months										
No history of severe hypoglycaemia^c^										
Baseline										
6 months										
12 months										
Personalised HbA1c target										
Personalised target^d^										
Baseline										
6 months										
12 months										
No personalised target^e^										
Baseline										
6 months										
12 months										

*CI* confidence interval

^b^HbA1c target is 8%

^c^ HbA1c target is the general HbA1c target of 7%

^d^ HbA1c target based on average of personalised HbA1c targets

^e^ HbA1c target is the general HbA1c target of 7%

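### The economic result is planned as a mean and 95% CI of the cost-per-QALY ratio, which becomes unreadable if the QALY difference is not clearly away from zero

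*SAP article*

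**What the plan says.** Under Secondary outcomes, the SAP article names the economic endpoint as "Incremental cost per quality-adjusted life year (QALY) for the intervention relative to control for the trial period". Under Economic evaluation it states "Costs and benefits will be bootstrapped" and that the results will be "presented as the mean and 95% confidence interval (CI) of the incremental cost per QALY gained at trial conclusion". The same paragraph adds "Simulated cost-effectiveness will be presented for r-CGM relative to the control via a cost-effectiveness plane and a cost-effectiveness acceptability curve", together with univariate and probabilistic sensitivity analyses.

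Table 5 is captioned as showing "mean differences and incremental cost-effectiveness ratios during the trial follow-up period for intervention vs control groups". It labels total health-system cost (1), total societal cost (2) and QALYs (3), and forms the two ICER rows as (1)/(3) and (2)/(3). The column headings cover a mean difference with 95% CI and a P value. The ICER rows sit under those headings, with nothing marking the cells as not applicable.

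The article does not say how a confidence interval for the ratio is to be formed, and it plans no net-benefit analysis.

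**The concern.** An ICER does not order results from good to bad once the QALY difference can take either sign. A negative ratio can mean cheaper and better (dominant) or dearer and worse (dominated). A positive ratio can mean dearer and better or cheaper and worse. Replicates with a QALY difference close to zero give very large ratios of either sign. Percentile limits taken over such values place opposite conclusions in the same tail, so the interval cannot be compared with a willingness-to-pay value. If the reported mean is the average of replicate ratios, it is driven by the few replicates nearest zero and does not settle as replicates are added.

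At stake is the stated numerical answer to a named secondary objective, cost-effectiveness. There is also an ambiguity: the mean in the Economic evaluation text could be computed as an average of bootstrap ratios, while Table 5 points to a single ratio. These are different estimators, and the text leaves the choice open.

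**Working it through.** **Design figure, for context on precision.** The trial was sized on HbA1c only: "Using a significance level of 0.05, power of 0.8, clinically significant difference of 0.5%, and standard deviation of 1.3% for HbA1c". By the normal formula, n = 2(1.96 + 0.8416)² × 1.3² / 0.5² = 106.1, so 107 per group. The t-based solution is 107.1, so 108. The stated 108 per group is reproduced, as are 216/0.8 = 270 and 270/0.9 = 300. The follow-up that bounds the QALY difference is short: "As the economic evaluation will be performed within a 12-month period, discounting will not be applied".

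**Assumptions.** The article gives no QALY SD, QALY difference, cost difference or cost SD. All such values below are assumed. Cost and QALY differences are drawn as independent normals.

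**Step 1: how often the QALY difference falls at or below zero.** SE(ΔQ) = SD × √(2/n) and P(ΔQ ≤ 0) = Φ(−ΔQ/SE). With n = 108 per group, √(2/108) = 0.1361:

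| True gain | SD 0.10 | SD 0.15 | SD 0.20 | SD 0.25 |
|---|---|---|---|---|
| 0.01 | 0.231 | 0.312 | 0.357 | 0.384 |
| 0.02 | 0.071 | 0.164 | 0.231 | 0.278 |
| 0.03 | 0.014 | 0.071 | 0.135 | 0.189 |
| 0.05 | <0.001 | 0.007 | 0.033 | 0.071 |

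With 150 per group and a gain of 0.02, the range is 0.042 to 0.244.

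**Step 2: one scenario in full.** Take 120 per arm (150 less 20% attrition), gain 0.02, QALY SD 0.20, incremental cost 600 with SE 500.
- SE(ΔQ) = 0.20 × √(2/120) = 0.0258. z = 0.775, so P(ΔQ < 0) = 0.219.
- P(ΔC < 0) = Φ(−600/500) = 0.115.
- Dominant: 0.115 × 0.781 = 0.090. Dominated: 0.885 × 0.219 = 0.194. Together 28% of ratios are negative, with opposite meanings.
- Cheaper but less effective: 0.115 × 0.219 = 0.025. These ratios are positive and mix with the dearer-and-better ones.
- Ratio of means: 600/0.02 = 30,000. Simulated percentile interval: about −288,000 to +311,000.
- Means of ratios in five batches of 40,000 draws ran from about 8,000 to 159,000 with one seed, and from about −35,000 to +27,000 with another.

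**Step 3: where the summary recovers.** In the same setting a gain of 0.08 gives z = 0.08/0.0258 = 3.1 and P(ΔQ < 0) = 0.1%. The interval is then about −5,000 to +30,000 around a ratio of means of 600/0.08 = 7,500, and one set of batch means ran from 7,900 to 9,500.

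A second set used 108 per group, ΔC = 1,000 and cost SD 5,000, with 1,000 draws repeated 20 times:

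| QALY SD, gain | Gain/SE | Ratio of means | Mean of ratios, range over 20 runs | Typical percentile interval |
|---|---|---|---|---|
| 0.15, 0.02 | 0.98 | 50,000 | −518,000 to +2,758,000 | −494,000 to +510,000 |
| 0.15, 0.05 | 2.45 | 20,000 | −73,000 to +167,000 | −9,000 to +93,000 |
| 0.10, 0.05 | 3.67 | 20,000 | 19,000 to 29,000 | −7,000 to +62,000 |
| 0.10, 0.08 | 5.88 | 12,500 | 12,300 to 13,500 | −4,300 to +32,000 |

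**Step 4: net monetary benefit in the Step 2 scenario.** NMB = λ × ΔQ − ΔC. The article gives no λ. For illustration take λ = 30,000, the ratio of means in Step 2. NMB = 30,000 × 0.02 − 600 = 0. SE = √((30,000 × 0.02582)² + 500²) = √(600,000 + 250,000) = 922. The 95% CI is 0 ± 1.96 × 922, or about −1,807 to +1,807. It is finite and ordered, and exists whatever the sign of ΔQ.

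**The case against.** The strongest reply has four parts.

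First, a reader might infer that the interval will be uninterpretable. The article does not support that. It gives no QALY or cost figures, and Step 3 shows a readable result when the gain is large relative to its SE. A small gain is plausible over 12 months in a trial sized for HbA1c, but that supports only that the failure may occur. The planned analysis is also a decision-analytic model with linear and generalised linear components, so its SEs and its cost–QALY correlation could differ from the simple simulation in either direction. This stands, and the point is conditional.

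Second, a reader might infer that the plan averages replicate ratios. The text does not say so. Read with Table 5, the mean may simply be the ratio of mean differences. This also stands: the instability of the mean applies only under the other reading. The interval problem does not depend on the reading.

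Third, a reader might infer that the trial would have no cost-effectiveness result usable against a threshold. That goes too far. The acceptability curve gives the probability of cost-effectiveness at each threshold and handles all four quadrants, the plane shows the mix of signs, and Table 5 gives the cost and QALY differences separately with CIs. These are valid, but they do not correct the ICER interval reported beside them.

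Fourth, an article may leave the interval method to a fuller document. That covers the choice between percentile and other methods. It does not cover the positive commitment to a mean and 95% CI of the ratio, made without condition. As for the P-value column, Table 5 is an empty shell. It does not prove that a P value for the ICER is intended, only that nothing rules one out.

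**Conclusion.** The point holds in conditional form. The plan commits to an ordinary mean and 95% CI for a ratio whose denominator may not be clearly away from zero, and it sets no rule for that case. Under the assumed gains of 0.01 to 0.03 with 108 per group, the probability of a QALY difference at or below zero is 1% to 38%. Where the gain was about one SE or less, the interval spanned several hundred thousand in both directions. At about 3 SE and above in the cases run, it was readable. The article cannot say which case will apply. This is a moderate reporting weakness in one secondary outcome, partly offset by the planned plane and acceptability curve. The primary HbA1c analysis is not touched.

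**What to change.** - In Economic evaluation, state that the ICER point estimate is the ratio of mean differences, as in Table 5, (1)/(3) and (2)/(3), and not the mean of bootstrap ratios.
- Give an interval for the ICER, for example by Fieller's method, only if the QALY difference is clearly away from zero, and fix that condition in advance. One workable form is that the 95% CI of the QALY difference excludes zero, which is also the condition for a bounded 95% Fieller interval. Otherwise report the point estimate with the plane.
- In Table 5, mark the P-value cells of the ICER rows as not applicable.
- Report incremental net monetary benefit with a bootstrap 95% CI over a stated range of willingness-to-pay values, for the health-system and societal perspectives, beside the planned plane and acceptability curve.

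The cost is small. A willingness-to-pay range has to be chosen and stated before the results are seen, and Table 5 gains two rows. The same bootstrap replicates serve, and no new data or change to the primary analysis is needed.

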#### Explanatory analysis

We will conduct two planned subgroup analyses for HbA1c at 6 and 12 months. In the first analysis, a two-way interaction term between history of severe hypoglycaemia (yes/no) and study group will be included in the primary analysis model to examine if there is a different intervention effect between those with a history of severe hypoglycaemia compared to those without. For the second subgroup analysis, a two-way interaction term between study group and type of HbA1c target (personalised vs general) will be added to the primary analysis model, to examine whether the intervention effect varies according to whether participants have a personalised HbA1c target that is different from the general target of 7% or not.

Results from the primary, secondary, and sub-analyses will be presented as shown in Tables 3, 4, 5, and 6. Estimates of the between-group difference for mean outcomes will be reported with their respective 95% confidence intervals and *p* values.

**Table 3 Tab3:** Estimated HbA1c and between-group differences for intervention and control groups

	Estimated mean HbA1c (95% CI)		Difference in estimated mean HbA1c and general HbA1c target of 7%		Unadjusted		Adjusted*	
	Intervention group (*n*=)	Control group (*n*=)	Intervention group (*n*=)	Control group (*n*=)	Intervention vs. Control between-group differences (95% CI)	*P* Value	Intervention vs. Control between-group differences (95% CI)	*P* Value
Baseline								
6 months								
12 months								

*Adjusted for age, IRSD and history of severe hypoglycaemia

**Table 4 Tab4:** Estimated percentage time in target, diabetes distress and between-group differences for intervention and control groups (secondary analyses)

	Estimated mean % time in target (95% CI)		Unadjusted		Adjusted*	
	Intervention group (*n*=)	Control group (*n*=)	Intervention vs. Control between-group differences (95% CI)	*P* Value	Intervention vs. Control between-group differences (95% CI)	*P* Value
Percentage time in target (%)						
Baseline						
12 months						
	Estimated mean diabetes distress (95% CI)		Unadjusted		Adjusted*	
	Intervention group (*n*=)	Control group (*n*=)	Intervention vs. Control between-group differences (95% CI)	*P* Value	Intervention vs. Control between-group differences (95% CI)	*P* Value
Diabetes-specific distress (PAID)						
Baseline						
12 months						

*Adjusted by age and IRSD

**Table 5 Tab5:** Mean and standard deviation (SD) costs, mean and SD quality-adjusted life years (QALYs), mean differences and incremental cost-effectiveness ratios during the trial follow-up period for intervention vs control groups (secondary analyses)

	Intervention mean (SD)				Control mean (SD)		Mean difference (95% CI) per patient			*P* value
Costs										
Intervention (A)										
Hospital utilization (B)										
Medical benefits (C)										
Pharmaceuticals (D)										
Patient costs (E)										
Total cost health system (A + B + C + D)						(1)				
Total cost societal (A + B + C + D + E)						(2)				
QALYs						(3)				
Incremental cost effectiveness ratio (ICER)										
Health system perspective						(1)/(3)				
Societal perspective						(2)/(3)				

*CI* confidence interval

**Table 6 Tab6:** Estimated glycated haemoglobin (HbA1c) and between-group differences by history of severe hypoglycaemia and personalised HbA1c target for intervention and control groups (sub-group analyses)

	Estimated mean HbA1c (95% CI)				Difference in estimated mean HbA1c and HbA1c target		Unadjusted		Adjusted^a^	
	Intervention group (*n*=)		Control group (*n*=)		Intervention group (*n*=)	Control group (*n*=)	Intervention vs. control between-group differences (95% CI)	*P* value	Intervention vs. control between-group differences (95% CI)	*P* value
Severe hypoglycaemia										
History of severe hypoglycaemia^b^										
Baseline										
6 months										
12 months										
No history of severe hypoglycaemia^c^										
Baseline										
6 months										
12 months										
Personalised HbA1c target										
Personalised target^d^										
Baseline										
6 months										
12 months										
No personalised target^e^										
Baseline										
6 months										
12 months										

*CI* confidence interval

^b^HbA1c target is 8%

^c^ HbA1c target is the general HbA1c target of 7%

^d^ HbA1c target based on average of personalised HbA1c targets

^e^ HbA1c target is the general HbA1c target of 7%

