#### Statistical modelling

##### Primary and secondary outcomes

Whilst our primary outcome is HbA1c at 12 months post-intervention, we will estimate the between-group difference in mean HbA1c at 6 and 12 months with the same linear mixed-effects model using restricted maximum likelihood estimation. As the data are longitudinal, HbA1c measured at baseline, 6 months, and 12 months will be included in the model as the dependent variable and study groups (intervention and control) and time of the pathology result (baseline, 6, and 12 months) will be collected as fixed effects. A two-way interaction term between study group and time will be included in the model to estimate the between-group difference in mean HbA1c at 6 and 12 months, but we will constrain the estimated baseline means to be equal. The model will include random intercepts for clinic (as individuals will be clustered within clinics) and individuals (as patient measures are repeated within individuals). An unstructured variance-covariance structure will be assumed for the random effects variables as correlations between measurements within individuals and correlations between measurements in participants from the same clinic are expected to be unique.

Age, index of relative socio-economic disadvantage (IRSD), and a history of severe hypoglycaemia are known to be at least moderately associated with HbA1c [9, 27]. In a secondary analysis, the outcome measure will be adjusted for these potential confounders. These measures will be included as fixed effects in the model.

An intention-to-treat (ITT) approach will be used where participants will be analysed according to the study group they were assigned, and all participants will be included in the analysis, consistent with mixed model analysis [28]. The estimated mean HbA1c levels at baseline, 6 months, and 12 months will be plotted for each study group with 95% confidence intervals.

The same statistical modelling approach described for HbA1c will be used for the secondary outcomes, percentage time in target and diabetes-specific distress at 12 months. Transformations for skewed outcome measures will be considered.

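### Both subgroup analyses add a group × subgroup term with no time component to a model that has baseline HbA1c as an outcome, so the term does not estimate effect modification at 6 or 12 months

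*SAP article*

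**What the plan says.** Under Primary and secondary outcomes, the SAP article defines a longitudinal model: "HbA1c measured at baseline, 6 months, and 12 months will be included in the model as the dependent variable". The treatment effect is carried by a visit-specific term: "A two-way interaction term between study group and time will be included in the model". The sentence goes on: "but we will constrain the estimated baseline means to be equal". The random effects are intercepts for clinic and for individual.

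Under Explanatory analysis the article announces: "We will conduct two planned subgroup analyses for HbA1c at 6 and 12 months". For the first, "a two-way interaction term between history of severe hypoglycaemia (yes/no) and study group will be included in the primary analysis model". For the second, "a two-way interaction term between study group and type of HbA1c target (personalised vs general) will be added to the primary analysis model". No term combining group, subgroup and time is named, nor is a subgroup × time term, and nothing limits the added term to visits after baseline. Table 6 has rows for baseline, 6 months and 12 months within each subgroup, with a between-group difference for each.

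**The concern.** In a model with baseline among the outcomes, the treatment effect lies in the group × time coefficients. To ask whether that effect differs by subgroup, the subgroup must interact with those coefficients. A group × subgroup term without time shifts the difference between arms by the same amount at all three visits, which has three consequences:

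- Baseline enters the estimate of effect modification, although randomisation makes the true value zero there.
- A non-zero coefficient means that the arms differ at baseline in at least one subgroup, which conflicts with the equal-baseline constraint.
- Modification at 6 months is forced to equal modification at 12 months, although the analyses are said to address both times and Table 6 reports by visit.

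These are the only two subgroup analyses in the plan. A diluted interaction could be read as evidence that the intervention works alike in everyone, and the subgroup differences in Table 6 would be biased.

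**Working it through.** **Inputs from the SAP article.** Three visits; group × time; baseline equal between arms; random intercepts; SD 1.3%; 300 participants planned; 20% participant attrition. The article gives no figure for the subgroup analyses, so there is none to reproduce.

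**Assumptions, not in the article.** Within-person correlation ρ from 0.3 to 0.7; subgroup prevalence 10% to 50%; clinic variance ignored; a subgroup main effect in the model. True modification is 0 at baseline, d6 at 6 months and d12 at 12 months. The time course is flat (d6 = d12), linear (d6 = d12/2) or late (d6 = 0).

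**Method.** With V = σ²[(1 − ρ)I + ρJ] for the three visits, and n, X and μ the size, design matrix and true means of each arm-by-subgroup cell, the expected coefficients are (Σ n X′V⁻¹X)⁻¹ Σ n X′V⁻¹μ.

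**Step 1: share of d12 that the added term captures.**

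If a free group main effect is kept, the coefficient is the plain mean over visits, (0 + d6 + d12)/3:
- flat: 2/3 = 0.67
- linear: 1.5/3 = 0.50
- late: 1/3 = 0.33

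If there is no group main effect, baseline equality holds only in the reference subgroup and the share depends on ρ and prevalence. The last row applies the term after baseline only and assumes no difference in trend between subgroups.

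| Coding of the added term | Flat | Linear | Late |
|---|---|---|---|
| All visits, free group main effect | 0.67 | 0.50 | 0.33 |
| All visits, no group main effect | 0.37–0.63 | 0.28–0.47 | 0.19–0.31 |
| After baseline only | 1.00 | 0.75 | 0.50 |

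**Step 2: effect on Table 6.** Take ρ = 0.5, prevalence 20%, d12 = −0.5%, flat course and no group main effect. The interaction coefficient is −0.286, so the fitted baseline difference in the non-reference subgroup is also −0.286%, where the truth is 0. With true 12-month differences of −0.5% (reference) and −1.0% (other subgroup), the fit gives −0.571% and −0.571 − 0.286 = −0.857%. The first is too large by 0.071 and the second too small by 0.143.

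**Step 3: power in one worked case.** Take 300 × 0.8 = 240 participants, prevalence 25%, ρ = 0.6, d12 = −0.6%. Two-sided power at the 5% level is about Φ(|b|/SE − 1.96).

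| Test | Coefficient (SE) | Power |
|---|---|---|
| All-visit term, no group main effect, flat | −0.321 (0.298) | 19% |
| Same, linear | −0.241 (0.298) | 13% |
| 12-month group × subgroup × time | −0.600 (0.310) | 49% |
| Pooled post-baseline term with subgroup × time, flat | −0.600 (0.257) | 65% |
| Same, linear | −0.450 (0.257) | 42% |

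**Step 4: the post-baseline coding without subgroup × time.** Use the same case with no effect modification at all, but let HbA1c in the subgroup fall by an extra 0.6% in both arms at 6 and 12 months. The post-baseline term has expectation −0.51 with SE 0.195. Then 0.51/0.195 ≈ 2.6 and Φ(2.6 − 1.96) ≈ 0.74, so a nominal 5% test rejects about 74% of the time. Once subgroup × time is added, the expected coefficient returns to 0. Differing trends are plausible: under Inclusion criteria, entry is at least 0.5% above a target of 7% or 8%, so entry levels, and with them regression to the mean, can differ between subgroups.

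**The case against.** The strongest reply is that the term is added to a model whose treatment effect exists only after baseline, and that the text speaks of 6 and 12 months and of a different intervention effect. An analyst who keeps the constraint would code the term after baseline only, and then neither the averaging with baseline nor the breach of the constraint arises. This is a fair reading, and a condensed article may use shorthand. It does not settle the matter. The article spells out its two-way terms, and the post-baseline version of the stated term still pools 6 and 12 months and is exposed to the false interaction in step 4.

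A second reply is that the missing subgroup × time term does no harm under the literal coding. That is correct: with arms balanced within subgroups, a common subgroup trend leaves the expected all-visit coefficient unchanged. The omission matters under the post-baseline coding.

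A third is that a 12-month test is not always the more powerful choice. With a flat effect, a pooled post-baseline term with subgroup × time has 65% power against 49%. This stands, and it is a real cost of the fix.

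A reader might also infer that the stated model cannot produce separate 6- and 12-month subgroup differences for Table 6. It can: group × time lets those differences vary by visit. Only the modification is forced equal, and the resulting differences are biased rather than missing.

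**Conclusion.** The subgroup model is wrong as written, in both places. Read literally, it conflicts with the equal-baseline constraint and dilutes 12-month effect modification; read charitably, it can create modification where there is none. The conflict with the constraint, the 6- and 12-month wording and the visit rows of Table 6 follows from the text alone.

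The size does not. The retained share of about 0.19 to 0.67 rests on the assumed time course, prevalence and correlation, and on whether a group main effect is kept. A reader might infer that any 12-month modification is roughly halved. One half is exact only for a linear build-up with a free group main effect, and the documents fix neither. Nor does the fix make these analyses well powered: in the worked case it reaches 49%, for an assumed modification of 0.6% that exceeds the 0.5% difference on which the trial was sized.

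The fault should be corrected but does not threaten the trial's main result. These are subgroup analyses, and the primary 12-month estimate, the sample size and the secondary outcomes are unaffected.

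**What to change.** For each subgroup analysis, state the model in full: subgroup, subgroup × time, and group × subgroup × time at 6 and 12 months, with the arms constrained to be equal at baseline within each subgroup. Name the 12-month three-way coefficient as the test of effect modification, report the 6-month coefficient beside it, and fill Table 6 from these contrasts.

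The cost is a few lines of SAP text and a few model terms; no new data are needed. The statistical price is lower power than a pooled post-baseline term if the modification is the same at both visits (about 49% against 65% in the worked case). If the authors prefer the pooled term, they should say so, apply it only after baseline and include subgroup × time.
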